**Methods/design:**

To determine whether the traditional Chinese medicine *Yi Shen Jian Gu* granules could effectively manage AIMSS we will conduct a multicenter, randomized, double-blind, placebo-controlled clinical trial. Patients experiencing musculoskeletal symptoms after taking AIs will be enrolled and treated with traditional Chinese medicine or placebo for 12 weeks. The primary outcome measures include Brief Pain Inventory-Short Form, Western Ontario and McMaster Universities Osteoarthritis Index, and Modified Score for the Assessment and Quantification of Chronic Rheumatoid Affections of the Hands, which will be obtained at baseline and at 4, 8, 12 and 24 weeks.

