### Randomization and blinding

Block randomization was carried out in a 1:1 ratio according to the sequence generated with SAS (Version 7.0; Channel-leadian pharmaceuticals R&D, Co., Ltd; [name]). Drug codes, numbered from 1 to 84, and contained group assignments will be generated according to randomization numbers. Eligible patients will be randomized into the YSJG group or the placebo group by obtaining medicines associated with the given drug codes in accordance with the order of visits. Group assignments will not be revealed until the entire study is completed. Participants, investigators, statisticians, and all study staff are blinded.

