### Sample size calculation

As there has been no similar TCM research on AIMSS to date, we calculated sample size according to another AIMSS study that used the same primary outcome measure (BPI-SF)
[18]. From the results of this previous study, the treatment group had a reduction of 1.5 points (the standard deviation was 2.1) on the mean BPI-SF worst pain compared with the control group. Therefore, 34 participants per group were deemed sufficient to achieve 90% power and a (one-sided) 5% significance level in detecting treatment differences. Considering a total withdrawal and dropout rate of 20%, we concluded that a total of 84 patients (42 per arm) would need to be recruited to ensure statistically significant results.

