### Statistical analysis

Efficacy and safety analyses will be conducted according to the intention-to-treat principle. Missing values will be imputed by the last-observation-carried-forward method. All statistical analyses will be performed using Statistical Packages of Social Sciences software (SPSS 18.0, Channel-leadian pharmaceuticals R&D, Co., Ltd; [name]). Statistical significance will be defined as a one-sided *P*-value of <0.05. Demographic, clinical, and outcome variables will be described using means and standard deviations for continuous variables and percentages for categorical variables. The primary analysis will be to compare the mean pain scores from BPI-SF, the WOMAC, and the M-SACRAH and the mean joint stiffness and function scores from the WOMAC and the M-SACRAH between the TCM group and the placebo group. The secondary analysis will be to compare the mean scores from FACT-B and changes in BMD before and after treatment. Student’s t-tests and repeated-measure analyses of variance with a time-interaction term will be used to compare group differences.

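### The plan requires a one-sided P-value, yet one of its two unranked tests, the group-by-time interaction, is an omnibus F test with no direction

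*Protocol article*

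**What the plan says.** Three statements bear on this point.

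- **Criterion** (Statistical analysis): "Statistical significance will be defined as a one-sided *P*-value of <0.05".
- **Methods** (Statistical analysis): Student's t-tests are named first, and then "repeated-measure analyses of variance with a time-interaction term will be used to compare group differences". The two are joined without a ranking. No visit is given as decisive, and the visits that enter the ANOVA are not listed.
- **Sizing** (Sample size calculation): the planning values are "a reduction of 1.5 points (the standard deviation was 2.1) on the mean BPI-SF worst pain", from which "34 participants per group were deemed sufficient to achieve 90% power and a (one-sided) 5% significance level in detecting treatment differences". No week is attached to the 1.5 points, and it is not said whether 2.1 is the SD of scores or of changes.

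The abstract says of the pain and joint scales, "which will be obtained at baseline and at 4, 8, 12 and 24 weeks". Under Study design, treatment lasts 12 weeks and a 12-week follow-up comes after it, so week 24 is off treatment.

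**The concern.** A one-sided criterion presupposes a statistic with a sign: evidence that YSJG is better than placebo, not merely different. A group-by-time interaction over several visits asks whether the two mean curves are parallel. It responds to any departure from parallel, in either direction and at any visit. Three things are at stake.

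1. The stated criterion cannot be applied to one of the two named tests.
2. If the t-test and the interaction disagree, the text does not say which one is the result.
3. If week 24 enters the ANOVA, divergence or loss of effect after treatment stops counts towards significance. The schedule makes this likely, but the article does not state it.

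**Working it through.** **Inputs from the article:** difference δ = 1.5, SD σ = 2.1, one-sided 5%, 90% power, n = 34 per arm, 1:1 allocation, visits at weeks 0/4/8/12/24.

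**Assumed, not in the article:** a constant within-patient correlation ρ of 0.3, 0.5 or 0.7; 2.1 read as the SD of scores; six time courses of the group difference, each reaching 1.5 at week 12.

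**Step 1: reproduce the sample size.** n = 2(z₀.₉₅ + z₀.₉₀)²σ²/δ² = 2(1.645 + 1.282)² × 4.41/2.25 ≈ 33.6, so 34 per arm. For the t-test, the noncentrality is 1.5/(2.1√(2/34)) = 2.945. With a one-sided critical value of 1.668 on 66 df, power is 0.898 (0.903 by the normal approximation). The stated figure is therefore right for one two-group, one-sided mean comparison.

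**Step 2: direction of the interaction.** With five visits, the test has 5 − 1 = 4 numerator df (3 over weeks 0–12). Under constant correlation its noncentrality is

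λ = (n/2) × S / (σ²(1 − ρ)), where S = Σ(d_t − d̄)².

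Here d_t is the group difference at visit t and d̄ is its mean over visits. The deviations are squared, so reversing the sign of every d_t leaves λ unchanged. The chance of significance is identical for a benefit and for the same-sized harm.

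**Step 3: power of the interaction.** The df are 4 and 4 × 66 = 264, and the 5% critical value is 2.406. Worked case, 0/0.5/1.0/1.5/0.75 at ρ = 0.5: d̄ = 0.75, S = 1.25, λ = 17 × 1.25/(4.41 × 0.5) = 9.64, power 0.69.

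| Difference at weeks 0/4/8/12/24 | S | ρ = 0.3 | ρ = 0.5 | ρ = 0.7 |
|---|---|---|---|---|
| 0/1.5/1.5/1.5/1.5 | 1.80 | 0.70 | 0.86 | 0.98 |
| 0/1.5/1.5/1.5/0 | 2.70 | 0.88 | 0.97 | 0.999 |
| 0/0.5/1.0/1.5/1.5 | 1.70 | 0.67 | 0.83 | 0.97 |
| 0/0.5/1.0/1.5/0.75 | 1.25 | 0.52 | 0.69 | 0.91 |
| 0/0.5/1.0/1.5/0 | 1.70 | 0.67 | 0.83 | 0.97 |
| 0/0/0/1.5/0 | 1.80 | 0.70 | 0.86 | 0.98 |

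Rows 1 and 2 show what week 24 does. An effect that vanishes after treatment raises power from 0.86 to 0.97 at ρ = 0.5, because the loss of effect is itself a departure from parallel curves.

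The choice of visits matters too. Over weeks 0–12 only, power at ρ = 0.5 is 0.74–0.86. If baseline is left out and the effect is constant from week 4, S = 0 and the rejection rate is just 0.05.

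**Step 4: a directional contrast.** For a week-12 comparison adjusted for baseline, the residual SD is 2.1√(1 − ρ²) = 2.00, 1.82 and 1.50 at ρ = 0.3, 0.5 and 0.7. The noncentralities are 3.09, 3.40 and 4.12. Against a one-sided critical value of 1.669 on 65 df, power is 0.92, 0.96 and 0.99. It does not depend on the time course at other visits.

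**The case against.** Student's t-tests are also named, so a directional test compatible with the one-sided rule is already in the plan. With baseline in the model, the interaction asks whether change over time differs between arms, a legitimate question in a longitudinal trial. A significant interaction would be read together with the group means, which show direction. The ANOVA's group main effect has 1 df and could be read one-sided. An article may also leave the choice of visits to the full protocol or SAP.

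Much of this stands, and it rules out several stronger readings that a reader might infer:

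- **That the interaction asks the wrong question.** It asks a non-directional one, which is a narrower fault.
- **That it has much less power than the planned comparison.** The article gives neither a correlation nor a time course, and the table runs from well below 0.90 to above it.
- **That the trial was sized for week 12.** The sample size section names no week; week 12 is an inference from the end of treatment.
- **That week 24 is in the ANOVA.** The collection schedule suggests it, but no sentence says so.
- **That unequal visit spacing invalidates the ANOVA through sphericity.** Spacing alone does not break sphericity, and a correction is ordinary SAP detail.

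The objection does not remove the conflict itself. The article states both a one-sided criterion and a test that cannot meet it. It ranks neither method and does not nominate the main effect as the term that decides. That is an inconsistency in the text as written, not a detail deferred to another document.

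**Conclusion.** The point holds in this form: the one-sided criterion and the group-by-time F test are incompatible, the test stands unranked beside t-tests, and it is not the comparison behind 34 per arm. None of this needs an assumption about correlation or time course.

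The size of the power consequence does need such assumptions. Under those listed, interaction power spans 0.52 to 0.999, against 0.898 for the planned comparison. It is lowest for gradual onset with partial loss by week 24 and low correlation. It exceeds 0.90 at every time course examined when ρ = 0.7. The fair description is that its power is unsecured by the sample size, not that it is low. The part about week 24 is conditional on that visit entering the model. The plan should be changed here, but the fault does not undermine the design.

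**What to change.** In the Statistical analysis section:

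1. Name one deciding test: a directional between-group contrast of BPI-SF worst pain at a stated visit. Week 12, the end of treatment, is the natural choice. Adjust it for baseline, either by ANCOVA or by a repeated-measures model with baseline as a covariate and not as one of the outcomes.
2. Report week 24 as a separate off-treatment contrast.
3. Keep the group-by-time interaction as supportive only, outside the one-sided criterion.
4. State in the sample size section that the 1.5 points refer to that visit, and whether 2.1 is the SD of scores or of changes.

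**Cost:** wording only, with no new data and no change in sample size. Power at 34 per arm is 0.92–0.99 for ρ of 0.3–0.7 if 2.1 is the SD of scores. If it is the SD of changes, a t-test on change already gives 0.898 and baseline adjustment should not lower it materially. There is a small downside: the second test no longer decides the result. The plan must also say whether the chosen model uses values filled by last-observation-carried-forward or replaces that rule.

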### Data collection and monitoring

This is a 24-week clinical trial, in which participants need to take research medication for 12 weeks, accept a 12-week follow-up, attend five assessment visits, obtain two sets of laboratory tests (safety assessments) and BMD analysis, fill in four sets of questionnaires at each visit, and stop taking other herbal medications (Table 
2).

**Table 2 T2:** Data collection schedule

	**Screening**	**Treatment**			**Follow-up**
Visit number	1	2	3	4	5
Week number	−2 to 0	4	8	12	24
Patient characteristics	✘				
Past history	✘				
AIMSS	✘				
ECOG	✘				
BPI-SF	✘	✘	✘	✘	✘
WOMAC	✘	✘	✘	✘	✘
M-SACRAH	✘	✘	✘	✘	✘
FACT-B	✘	✘	✘	✘	✘
Bone mineral density	✘			✘	
Safety assessment	✘			✘	
Combined medication	✘	✘	✘	✘	✘
Adverse events		✘	✘	✘	✘
Compliance		✘	✘	✘	

AIMSS, aromatase inhibitor-associated musculoskeletal symptoms; BPI-SF, Brief Pain Inventory-Short Form; ECOG, Eastern Cooperative Oncology Group; FACT-B, The Functional Assessment of Cancer Therapy-Breast; M-SACRAH, Modified Score for the Assessment and Quantification of Chronic Rheumatoid Affections of the Hands; WOMAC, Western Ontario and McMaster Universities Osteoarthritis Index.

Beijing Qihuang Medicine Clinical Research Center is responsible for quality control. Censors have regular visits (once a month) to monitor protocol violations, the recruitment rate, AEs and participant compliance.

## Discussion

Up to half of patients on AI therapy experience musculoskeletal symptoms, and up to 20% will discontinue therapy because of intolerable side effects; therefore, AIMSS has become an important clinical issue requiring effective management.

Effective management of AIMSS is still a mystery in clinical practice, as the mechanisms behind AIMSS are not clearly understood. A number of small interventional trials investigating acupuncture
[19,20], vitamin D
[18], glucosamine
[21], short-term low-dose prednisolone
[22], thymosin α1
[23], duloxetine
[24] and yoga
[25] have provided various treatment strategies. However, most of these trials have had some methodological and practical limitations, including small sample sizes, larger-than-anticipated drop-out, a single-center design, lack of control group and blinding, and a short follow-up period. Therefore, developing appropriate management strategies for AIMSS will require further investigation. To date, there is still a lack of prospective, randomized, controlled trials to provide powerful evidence supporting the use of various treatment modalities. Our study will be the first randomized, double-blind, placebo-controlled clinical trial analyzing the efficacy and safety of TCM in patients with AIMSS.

There are several limitations to our study. One limitation is the absence of specific measures for AIMSS. AIMSS is a set of symptoms involving the bone, muscles and joints. There are no questionnaires specially designed for AIMSS. Through reviewing the literature and reported studies
[20,23,26], rheumatological questionnaires may be validated in the longitudinal assessment of joint symptoms, although the pathological processes are likely to be different. We selected WOMAC and M-SACRAH that focus on joint pain, stiffness, and functional status in the hands and knees, which are the most common locations of pain. Another limitation is the indeterminate diagnostic criteria of AIMSS. Musculoskeletal symptoms are reported according to different terms (for example, arthralgia, joint symptoms, joint pain, and musculoskeletal symptoms) in the literature. Because of the lack of clear diagnostic criteria, various clinical trials have reported a wide range of AIMSS incidence and research objects, which confuses physicians and investigators and makes it challenging to recognize the manifestations of AIMSS and to establish acceptable inclusion criteria. In order to clear the clinical characteristics of AIMSS and inclusion criteria, we defined AIMSS, through reviewing the literature
[10,11,27,28], as self-reported ongoing musculoskeletal symptoms, including arthralgia, joint stiffness, joint swelling, bone pain, myalgia, carpal tunnel syndrome, and trigger finger, which started or worsened after taking an AI.

The results of this study will provide a new evidence-based treatment strategy for patients suffering from AIMSS.

## Trial status

The trial is currently enrolling participants.

## Abbreviations

AE: Adverse event; AI: Aromatase inhibitor; AIMSS: Aromatase inhibitor-associated musculoskeletal symptoms; BMD: Bone mineral density; BPI-SF: Brief Pain Inventory-Short Form; ECOG: Eastern Cooperative Oncology Group; FACT-B: The Functional Assessment of Cancer Therapy-Breast; M-SACRAH: Modified Score for the Assessment and Quantification of Chronic Rheumatoid Affections of the Hands; TCM: Traditional Chinese medicine; WOMAC: Western Ontario and McMaster Universities Osteoarthritis Index; YSJG: *Yi Shen Jian Gu* granules.
